### Data monitoring and statistical analysis

To minimize measurement bias arising from multiple evaluators, clinical indicator assessments and laboratory tests for each patient before, during, and after treatment will be conducted by the same specialized physician whenever possible. The physician evaluating the laboratory indicators will be blinded to the group assignments and treatment. To avoid missing or incorrect data, clinical and laboratory indicator evaluations will be conducted according to preset time points and entered into the electronic database promptly.

Data management and analysis will be performed using IBM SPSS Statistics Version 26 (IBM SPSS Inc., Chicago, United States). The principles of data processing are as follows: measurement data will be expressed as mean ± standard deviation (
$\bar{x}$
± S); if count data are normally distributed, the chi-square test will be used; if data in the two groups are normally distributed, t-test, repeated-measures analysis of variance (ANOVA), and multivariate linear regression will be used for comparative analyses; if count data are not normally distributed, the Mann–Whitney U test will be used; *p* < 0.05 will indicate statistically significant differences.

We will use the last observation carried forward (LOCF) method, which replaces missing data points with the patient’s last observed value. In order to provide a more comprehensive assessment of the treatment effects in this study, we will conduct both an intention-to-treat (ITT) analysis and a per-protocol (PP) analysis.

We will implement the Bonferroni correction during statistical analysis to rigorously control Type I error rates, thereby ensuring methodological stringency in accordance with your recommendation.

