**Methods:**

Sixty-six patients with acute ischemic stroke will be randomly assigned 1:1 to control (conventional basal therapy, *n* = 33) and acupuncture (conventional standard stroke care + acupuncture, *n* = 33) groups for 10 days of intervention. The primary outcome is NIHSS score. The secondary outcomes: BMI and mRS scores, the level of TNF-A and IL-1B in serum, vascular endothelial growth factor (VEGF), Endocan ES, CD14+ and CD14- levels of peripheral blood mononuclear cells.

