### Sample size

Based on a review of previous research literature and the sample size calculation formula Health Statistics (14), equivalence tests were used to estimate the sample size. After 2 weeks of treatment, the NIHSS score for 63 patients in the observation group (conventional drug + acupuncture) was 7.53 ± 4.04, while the score for 63 patients in the control group (conventional drug only) was 12.61 ± 5.86. To calculate the sample size using an independent samples t-test, we need: effect size (Cohen’s d), significance level (*α*), power (1-*β*), and degrees of freedom (df). Cohen’s d is used to calculate the effect size, and the formula for Cohen’s d is: 
$d=\frac{M1-M2}{{SD}_{\mathrm{pooled}}}$
. For the observation group (conventional medication + electroacupuncture treatment): mean M1 = 7.53, standard deviation SD1 = 4.04, and for the control group (conventional medication): mean M2 = 12.61, standard deviation SD2 = 5.86. The pooled standard deviation (SDpooled) is known to be 5.62. Substituting into the formula, we obtain d ≈ −0.9, which represents a large effect size. When calculating the sample size using power analysis, the effect size d = 0.9, the significance level is typically set at *α* = 0.05, and the power 1 − *β* = 0.9. The formula for the independent samples t-test is: 
$n=\frac{2{\left(\upsilon_{\alpha }+\upsilon_{\beta }\right)}^{2}\sigma^{2}}{\delta^{2}}$
. With α = 0.05, β = 0.1, and a bilateral test, u₀.₀₅ = 1.96, u₀.₁ = 1.28, it was assumed that the control and treatment groups had equal therapeutic effects, with a combined 
$s=\sqrt{\frac{\left(n_{1}-1\right)s_{1}^{2}+\left(n_{2}-1\right)s_{2}^{2}+\frac{n_{1}n_{2}}{n_{1}+n_{2}}{\left({\bar{x}}_{1}-{\bar{x}}_{2}\right)}^{2}}{n_{1}+n_{2}-1}}$
 standard deviation of 
σ=5.62
. The mean difference between the two groups was substituted into the formula 
$n=\frac{2{\left(1.96+1.28\right)}^{2}\times 5.62^{2}}{{\left(12.61-7.53\right)}^{2}}=25.7\approx 26$
, resulting in a sample size of 26 patients for each group, resulting in a total of 52 patients across both groups (15). Based on the Guiding Principles for Clinical Research of New Chinese Medicines, and accounting for a 20% dropout and follow-up rate, a total of 66 patients should be included.:33 patients in the control group (basic treatment) and 33 patients in the treatment group (basic treatment + acupuncture) (16).

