### Outcome measurement

Clinical indicators will be conducted uniformly by professional physicians or therapists. NIHSS scores will be assessed once before treatment (Day 1), during treatment (Day 5), and after treatment (Day 10). BMI and mRS scores will be assessed before treatment (Day 1) and after treatment (Day 10).

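### The test rule attaches normality to the wrong data type and leaves the primary NIHSS analysis open among three methods, with no visit or baseline adjustment named

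*Protocol article*

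**What the plan says.** All statements are in the Protocol article.

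- **Categorical data** (Data monitoring and statistical analysis): "if count data are normally distributed, the chi-square test will be used", and "if count data are not normally distributed, the Mann–Whitney U test will be used".
- **Normally distributed data** (same section): "if data in the two groups are normally distributed, t-test, repeated-measures analysis of variance (ANOVA), and multivariate linear regression will be used for comparative analyses". No outcome, visit, order of methods or covariate is given.
- **Non-normal measurement data**: no test is named.
- **Multiplicity** (same section): a Bonferroni correction is promised, without a family of tests or a divisor.
- **Primary outcome** (abstract, Methods): "The primary outcome is NIHSS score". Outcome measurement schedules NIHSS on Days 1, 5 and 10. Neither place says which visit is primary, or whether the quantity compared is the score, its change or a baseline-adjusted score.
- **Sample size**: an independent-samples t-test on a post-treatment score, two-sided alpha 0.05 and power 0.90, using results after 2 weeks of treatment in earlier research.

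**The concern.** There are two faults in what the text states.

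First, the rule pairs tests with the wrong kind of data. Categorical counts are not normally distributed and chi-square does not ask them to be, so a literal reader would send every categorical outcome to a rank test. Measurement data that fail normality have nowhere to go. That could affect the blood markers (TNF-α, IL-1β, VEGF, ES), whose concentrations may be skewed.

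Second, the general rule is the only one that reaches NIHSS, and it offers several analyses side by side. They do not test the same hypothesis: a t-test at one visit, a group effect averaged over visits, a group-by-time interaction and a baseline-adjusted regression can give different p-values on the same data. If none is named in advance, the main result can be chosen after the data are seen, and the nominal 5% error rate no longer describes it.

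**Working it through.** **1. Reproduce the plan's sample size.** Inputs from Sample size: means 7.53 and 12.61 (difference 5.08), SD 5.62, normal quantiles 1.96 and 1.28.

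n = 2 × (1.96 + 1.28)² × 5.62² / 5.08² = 2 × 10.498 × 31.584 / 25.806 = 25.7, so 26 per group. With 20% dropout, 26 / 0.8 = 32.5, so 33 per group and 66 in total. The plan's figures are reproduced.

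**2. Set the test rule against the data types.**

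| Data type | Test under the rule as written | Comment |
|---|---|---|
| Categorical, called normal | Chi-square | The condition cannot be met and is not needed |
| Categorical, called non-normal | Mann–Whitney U | Does not suit nominal categories |
| Measurement, normal | t-test, repeated-measures ANOVA and regression | No primary method, visit or covariates |
| Measurement, non-normal | None | Possibly the blood markers |

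**3. Type I error if the smallest p-value is used.** Simulation under no effect: 26 per group, three visits, normal data, SD 5.62, equal correlation ρ between visits (assumed 0.5, 0.7 or 0.8), 20,000 replicates for each ρ. Each test alone rejects in about 5%.

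| Smallest p-value among | Type I error across ρ |
|---|---|
| Day 10 t-test, group-by-time interaction, baseline-adjusted regression | 0.107 to 0.113 |
| The same plus the repeated-measures group effect | 0.128 to 0.134 |

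**4. How far the listed methods differ.** Same set-up, 5,000 replicates, true difference 5.08 at Day 10 and, by assumption, half of it at Day 5.

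| Analysis | Power at ρ = 0.5 / 0.7 / 0.8 |
|---|---|
| Day 10 t-test | 0.90 / 0.90 / 0.89 |
| Repeated-measures group main effect | 0.49 / 0.44 / 0.40 |
| Group-by-time interaction | 0.83 / 0.97 / 1.00 |
| ANCOVA, Day 10 on Day 1 | 0.96 / 0.99 / 1.00 |

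The group main effect is weak because it averages in Day 1, before any treatment. With effects 0, D/2 and D at the three visits, the average is (0 + D/2 + D)/3 = D/2.

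**5. What baseline adjustment adds.** The ANCOVA residual SD is 5.62 × √(1 − ρ²): 4.87 at ρ = 0.5 and 4.01 at ρ = 0.7. Noncentral-t power with 26 per group (50 degrees of freedom unadjusted, 49 for ANCOVA):

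| True difference | Unadjusted t-test | ANCOVA, ρ = 0.5 | ANCOVA, ρ = 0.7 |
|---|---|---|---|
| 5.08 (planned) | 0.89 | 0.96 | 0.99 |
| 3 (assumed) | 0.47 | 0.59 | 0.75 |

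The documents give neither ρ nor a 3-point effect; both are assumptions.

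**The case against.** The strongest reply is that the wording is merely garbled. The second mention of count data is plausibly a slip for measurement data, which would supply the missing test, and chi-square on ordinary categorical counts is valid whatever condition is attached to it. That is fair. A reader might infer that the trial's categorical tests will be invalid, and the documents do not show that. The sentence is still wrong as published, and guessing its intent is not pre-specification.

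Second, the rule does not name NIHSS, and the sample size rests on a t-test of a post-treatment score, which points to a simple comparison after treatment. This is an anchor but not a commitment. The planning score was taken after 2 weeks, which is not a visit in this trial, and the analysis section adds two further methods without ranking them.

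Third, Bonferroni is promised. It would contain the inflation only if its family included the competing NIHSS analyses, and no family is given.

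Fourth, a reader might infer that repeated-measures ANOVA halves the effect and is unsuitable. That applies only to the group main effect. The text does not say that effect will be tested, and the group-by-time interaction performs far better.

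Fifth, detailed models and covariates are commonly left to an analysis plan. That is accepted for the secondary outcomes. It does not cover a stated rule that is wrong, or a primary outcome with several analyses listed and none chosen.

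**Conclusion.** The point holds in two parts, neither of which needs an assumed correlation: the data-type wording is wrong, and no single primary NIHSS analysis is fixed.

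The size of the second part is a type I error of about 0.11 to 0.13 if the most favourable analysis were reported. This rests on normal data, equal correlations of 0.5 to 0.8 and 26 per group. It shows what the open wording permits; nothing in the documents says the investigators intend to choose in this way.

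A reader might also infer that the trial lacks power without baseline adjustment. The documents do not support that: at the planned difference and SD the unadjusted t-test has 0.89. The gain from ANCOVA is a free improvement. It becomes large only if the true effect is smaller than planned, for example 0.47 against 0.59 to 0.75 at an assumed 3 points.

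**What to change.** 1. Name one primary analysis: Day 10 NIHSS by ANCOVA with Day 1 NIHSS as covariate, reporting the adjusted difference and its 95% confidence interval. Make Day 5 and all other NIHSS analyses secondary.
2. If repeated-measures ANOVA including Day 1 is kept as a secondary analysis, state that the group-by-time interaction is the test of treatment, not the group main effect.
3. For categorical data, use chi-square, or Fisher's exact test where expected counts are small, and remove the normality condition.
4. For ordinal or skewed measurement data, use Mann–Whitney or a suitable transformation.
5. State which tests the Bonferroni correction covers.

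The cost is wording only. Day 1 NIHSS is already scheduled, linear regression is already among the listed methods, and no visit or patient is added. The change should be made before any unblinded data are seen.

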### Secondary results

Activities of Daily Living: Modified Barthel Index (MBI); The Modified Barthel Index (MBI) (21, 22) is used to assess a patient’s functional status in activities of daily living (ADLs), with individual scores based on a series of independent behavioral measurements and a total score ranging from 0 to 100. The Barthel Index developed in 1965 by American researchers Dorothea Barthel and Florence Mahoney, is a widely used tool for assessing ADLs in rehabilitation settings, particularly in the United States. Barthel Index Assessment Criteria:

60 points or more: Mildly disabled, but essentially independently.40 to 60 points: Moderately disabled, requiring assistance with daily activities.20 to 40 points: Severely disabled, requiring significant assistance with daily activities.Less than 20 points: Totally disabled, completely dependence.

Assessment of Disability: The Modified Rankin Scale (mRS) (23, 24) is used to assess neurological recovery in stroke patients. mRS Scoring Criteria:

0 points: Asymptomatic; mild symptoms may be present, but the patient has not experienced any new functional limitations after the stroke.1 point: Symptoms are present, but there is no significant disability; the patient can complete all regular responsibilities and activities.2 points: Mild disability; the patient cannot perform all previously completed activities but can manage personal affairs independently.3 points: Moderate disability; the patient requires some assistance but can walk independently.4 points: Severe disability; the patient is unable to walk without assistance and cannot attend to their own physical needs.5 points: Severe disability; the patient is bedridden and incontinent, requiring constant care and attention. Although a trained nurse is not necessary, the patient needs someone to assist them several times throughout the day and night.

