### Follow-up

Patients will be followed up at 1 and 3 months post-discharge, with assessments of daily living ability (using the MBI scale) and disability (using the mRS scale).

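### LOCF is fixed for a missing Day 10 NIHSS although patients leave the trial because they deteriorate, and the termination rule conflicts with the promised ITT analysis

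*Protocol article*

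**What the plan says.** Under Data monitoring and statistical analysis, the protocol article fixes one rule for missing values: "We will use the last observation carried forward (LOCF) method". The same section promises that "we will conduct both an intention-to-treat (ITT) analysis and a per-protocol (PP) analysis".

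Outcome measurement gives the schedule of the primary outcome: "NIHSS scores will be assessed once before treatment (Day 1), during treatment (Day 5), and after treatment (Day 10".

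Termination criteria lists progression that leads to intensive care, serious reactions or events that hinder recovery, withdrawal by patient or family, intolerance to electroacupuncture or marked drug toxicity, and clinician judgement. Its opening sentence takes such patients out of the study. It does not say whether they are still scored, or whether they remain in the ITT set.

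Sample size raises 52 patients to 66, "accounting for a 20% dropout and follow-up rate".

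For the mRS, a secondary outcome, the in-hospital schedule is "BMI and mRS scores will be assessed before treatment (Day 1) and after treatment (Day 10", and then "Patients will be followed up at 1 and 3 months post-discharge". The printed scale starts at 0 and its last category is "5 points: Severe disability; the patient is bedridden and incontinent, requiring constant care and attention". No value is given for death.

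**The concern.** LOCF assumes that a patient's score would have stayed where it was last seen. The trial is designed to detect a change between Day 1 and Day 10, and some listed reasons for leaving are themselves bad outcomes. For a patient moved to intensive care, the last NIHSS predates the worsening, yet LOCF would enter it as the Day 10 result. The article names prevention of further progression as an aim, so the method could hide the event that the trial hopes to reduce. A patient who leaves while improving has the opposite error: later recovery is hidden.

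The errors need not cancel between arms, because electroacupuncture intolerance can end participation in one arm only. In addition, a single filled-in value is analysed as if it had been measured, so the standard error ignores the missing information. At stake are the size of the primary effect, its precision and, if freezing is unequal, the type I error.

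**Working it through.** **1. The plan's own figure.** Inputs from Sample size: means 7.53 and 12.61 (difference 5.08), SD 5.62, two-sided α 0.05, power 0.90, 20% loss.

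n = 2 × (1.96 + 1.28)² × 5.62² / 5.08² = 25.70, so 26 per arm. 26 / 0.8 = 32.5, so 33 per arm and 66 in total. The stated figures reproduce.

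**2. How many values, and what fills them.** 20% of 33 is 6.6, so up to about 7 patients per arm (66 − 52 = 14 overall). With three NIHSS visits, the value carried to Day 10 can only come from Day 1 or Day 5.

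**3. Dilution when both arms lose the same share.** Let m be the share carried forward and f the share of the treatment effect already present at the last score. Both are assumptions; the article gives neither.

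Difference = 5.08 × (1 − m + m × f). SE = 5.62 × √(2/33) = 1.384. Power = Φ(difference / SE − 1.96), with the SD held at 5.62.

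| m | f | Difference | Power at 33 per arm |
|---|---|---|---|
| 0 | – | 5.08 | 95.7% |
| 10% | 0.5 | 4.83 | 93.7% |
| 10% | 0 (Day 1) | 4.57 | 91.1% |
| 20% | 0.5 | 4.57 | 91.1% |
| 20% | 0 (Day 1) | 4.06 | 83.6% |

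For comparison, 26 observed patients per arm with no dilution give 90.3%. The worst row is therefore below the planned 90%, even though LOCF keeps all 33 per arm in the denominator.

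**4. Shift when patients in one arm are frozen before worsening.** For k patients whose true Day 10 score is w points above the carried one, the arm mean is too low by k × w / 33. Both k and w are assumed. The error rate with no true effect is Φ(−1.96 + b/SE) + Φ(−1.96 − b/SE), where b is the shift.

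| k | w = 4 to 10: shift in points | Share of 5.08 | Two-sided error at nominal 5% |
|---|---|---|---|
| 1 | 0.12 to 0.30 | 2% to 6% | not computed |
| 3 | 0.36 to 0.91 | 7% to 18% | 5.8% to 10.1% |
| 7 | 0.85 to 2.12 | 17% to 42% | 9.4% to 33.5% |

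**5. Would a mixed model alone repair this?** Take three patients in one arm who have only a Day 1 score and then worsen by 8 points, in an arm that otherwise improves by 3 (assumed). LOCF error in the arm mean: 3 × 8 / 33 = 0.73. A missing-at-random model predicts that they recover like the others, so the error is 3 × (8 + 3) / 33 = 1.00. The model removes the dilution in step 3, but not the hidden worsening in step 4. That needs observed scores after termination, or an explicit poor-outcome analysis.

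**6. Death on the mRS.** If death is scored 6 (assumption), each death carried at a last score of 2 to 5 lowers a 33-patient arm mean by (6 − 2)/33 = 0.12 to (6 − 5)/33 = 0.03.

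**The case against.** The strongest reply is that the sizes rest on invented inputs. The 20% combines dropout with follow-up loss and may include patients lost only at 1 or 3 months, when NIHSS is not scheduled. This stands: 14 of 66 is a ceiling, not a forecast of imputed primary values. It also stands that step 4 gives the shift in one arm. It equals the bias in the treatment difference only if the other arm has no such patients.

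A second reply is that a separate analysis plan may hold sensitivity analyses and a rule for death. This too stands, and the absence of a sensitivity analysis is not the point here. LOCF, however, is a stated choice, and so is the sentence that takes terminated patients out of the study.

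A reader might also infer more than the article supports:

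- That NIHSS changes from day to day. The article does not say so. It shows three visits and a planned difference after treatment.
- That controls go home early because they have no daily sessions. Discharge timing is not discussed; both arms are inpatients, basic medication runs for 10 days in both, and the Day 10 score is scheduled without distinction by arm.
- That terminated patients certainly enter the analysis with a wrong score. The article leaves open whether they enter it at all.
- That a death will be counted as mild disability. Carrying forward after death is inferred from LOCF being the only stated rule, and a last score of 2 is the extreme case. No death rate is given.

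**Conclusion.** The concern holds in this form: LOCF is a poor stated choice for Day 10 NIHSS, and it collides with a termination rule that removes patients for deteriorating. Followed as written, the plan either reports a score from before the event or abandons ITT, so the two sections must be reconciled. Standard errors are wrong wherever values are filled in, and the direction of the bias is not known.

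The size depends on the assumptions shown. At the 20% ceiling, with every carried score from Day 1, power falls from 95.7% to 83.6%; at the same ceiling with half the effect present at the last score, it falls to 91.1%. Three one-sided freezings of 4 to 10 points move an arm mean by 0.36 to 0.91 points. The mRS gap is minor: a secondary outcome, and at most 0.12 points per death in an arm mean over last scores of 2 to 5.

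This should be fixed before the data are unblinded. It does not undermine the design or the sample size.

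**What to change.** 1. Reconcile Termination criteria with the ITT commitment. State that terminated patients remain in the ITT set and that their scheduled Day 5 and Day 10 NIHSS is still recorded wherever possible. This concerns data collection only, not when treatment stops.
2. Make the primary analysis a likelihood-based mixed model on Day 5 and Day 10 NIHSS with Day 1 NIHSS as covariate, or multiple imputation by arm. Keep LOCF at most as a sensitivity analysis.
3. Both methods assume data missing at random, so add a sensitivity analysis that gives a poor outcome to patients who died or left because of deterioration. It can be a delta adjustment or a separate rank-based analysis with worst rank. A worst rank cannot sit inside a likelihood model on raw scores, so the two analyses must be kept apart.
4. As a minor addition, score death as mRS 6 at the 1- and 3-month visits, so that no death is carried forward as a living score.

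The cost is revised analysis wording, one added mRS code, somewhat more analysis work and a few extra assessments of patients who stopped early. The sample size does not change.

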In pain management, its mechanisms are focused on peripheral and central pathways, including reducing pain transmission and enhancing the release of endogenous opioids. In the fields of cancer pain, neurological diseases, and post-stroke recovery, acupuncture demonstrates increasing therapeutic advantages, not only improving the quality of life for patients but also offering more treatment options. However, the clinical application of acupuncture still faces many challenges, including the need for more clinical studies to further validate its efficacy and mechanisms.

The aim of this study is to determine whether acupuncture could improve vascular function in patients with AIS, thereby reducing NIHSS scores and preventing further disease progression. In this randomized controlled trial, we aim to improve patients’ neurological function and daily living abilities through acupuncture. To achieve this, we selected a series of scales and outcomes to comprehensively assess the efficacy of acupuncture. To objectively assess stroke severity, we selected the NIHSS as the primary outcome, a scale that comprehensively evaluates patients’ stroke conditions. To assess the quality of daily life, we employee the Modified Barthel Index (MBI) and the Modified Rankin Scale (mRS) as secondary outcomes.

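### Bonferroni is stated without a family or level and no primary NIHSS visit is named, so the success criterion is open; if the correction covers the primary test, the sample size does not allow for it

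*Protocol article*

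**What the plan says.** All places are in the protocol article.

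- **Data monitoring and statistical analysis, threshold.** A p-value below "0.05 will indicate statistically significant differences". The rule is not limited to any outcome.
- **Same section, last paragraph.** "We will implement the Bonferroni correction during statistical analysis to rigorously control Type I error rates". No family, number of tests or adjusted level follows, and the text does not say whether the primary test is included.
- **Sample size.** One two-group NIHSS comparison is sized "With α = 0.05, β = 0.1, and a bilateral test". No part of alpha is set aside for other tests.
- **Abstract, Methods.** "The primary outcome is NIHSS score". The Discussion repeats this, also without a visit: "we selected the NIHSS as the primary outcome, a scale that comprehensively evaluates patients’ stroke conditions".
- **Outcome measurement.** "NIHSS scores will be assessed once before treatment (Day 1), during treatment (Day 5), and after treatment (Day 10"). That gives two post-baseline visits.
- **Source of the planning effect (Sample size).** "After 2 weeks of treatment, the NIHSS score for 63 patients in the observation group". Two weeks is neither Day 5 nor Day 10.

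**The concern.** The article gives three rules that bear on success: a significance threshold, a multiplicity correction and a sizing alpha. Together they do not fix one criterion for the primary outcome. Two analysts could both follow the text and disagree on whether the trial succeeded. One might test Day 10 NIHSS at 0.05, another might split alpha between Day 5 and Day 10, and a third might divide it across every listed outcome.

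The unnamed visit adds to this. With NIHSS read at Day 5 and Day 10, and with a t-test, repeated-measures ANOVA and regression all listed as methods of comparison, the primary contrast could be picked once the data are known. If alpha were split to guard against that, the sample size makes no allowance for the split.

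**Working it through.** **Inputs (Sample size section).** Means 7.53 and 12.61, so the difference is 12.61 − 7.53 = 5.08. Group SDs are 4.04 and 5.86, with 63 per group in the earlier study. The planning SD is 5.62, alpha is 0.05 two-sided and power 90%. The plan has 26 per arm before dropout and 33 per arm enrolled.

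**The plan's own figure.** n = 2(1.96 + 1.28)² × 5.62² / 5.08² = 25.70, so 26 per arm. Allowing for 20% dropout, 26 / 0.8 = 32.5, so 33 per arm and 66 in total. The stated size reproduces for a single test at 0.05.

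**Which SD.** The SD formula in the article includes the between-group term: √[(62 × 4.04² + 62 × 5.86² + 31.5 × 5.08²) / 125] = 5.62. This is a total SD. The within-group SD from the same figures is √[(4.04² + 5.86²) / 2] = 5.03. It is the relevant SD for a t-test and gives higher power, so both are shown.

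**Power if the correction includes the primary test.** The test is run at 0.05/k. Power comes from the noncentral t distribution with 2n − 2 degrees of freedom and noncentrality (5.08/SD) × √(n/2). For SD 5.62 and n = 26, the noncentrality is 0.904 × √13 = 3.26.

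The document gives no k, so these values are assumptions:
- k = 1: the primary test stands alone (0.05).
- k = 2: Day 5 and Day 10 NIHSS (0.025).
- k = 9: NIHSS, MBI, mRS, TNF-α, IL-1β, VEGF, ES, CD14+ and CD14− (0.0056), taking the abstract's BMI to be the Modified Barthel Index described later.

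| SD | n per arm | k = 1 | k = 2 | k = 9 |
|---|---|---|---|---|
| 5.62 | 26 | 89.2% | 82.5% | 64.1% |
| 5.62 | 33 | 95.1% | 91.3% | 78.5% |
| 5.03 | 26 | 94.6% | 90.4% | 76.6% |
| 5.03 | 33 | 98.1% | 96.2% | 88.6% |

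The normal approximation, which is the plan's own method, gives 90.3%, 84.6% and 68.7% for the first row. By that method, 90% power at SD 5.62 would need 31 evaluable per arm for k = 2 and 41 for k = 9, against the planned 26.

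**The case against.** A reader might infer that the correction covers every test, that it contradicts the p < 0.05 rule, and that the stated 90% power is therefore lost. The documents do not support any of these.

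- **Scope.** The text does not say that primary and secondary outcomes share one alpha. A correction confined to secondary outcomes, or to follow-up visit contrasts after a repeated-measures model, fits the wording equally well. In either case the primary test keeps 0.05 and its sized power.
- **Threshold.** A Bonferroni-adjusted p-value is itself compared with 0.05, so the two sentences can both hold. The rule is undefined, not contradictory.
- **Power.** The loss is conditional. At k = 2 power stays above 90% if all 33 per arm are analysed, which LOCF with an ITT analysis makes possible, or if the within-group SD is used.
- **Unnamed visit.** This does not itself lower power; it permits selection. The planning effect is an end-of-treatment value, which points towards Day 10 without naming it.
- **Uncontrolled error.** It is also tempting to read the p < 0.05 rule as leaving all tests uncorrected and to quote the resulting family-wise error. The plan says that it will correct, so such figures would describe an analysis that it disclaims. They would also assume independence among plainly correlated outcomes.

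All of that stands. A last argument is that families and adjusted levels are commonly left to a statistical analysis plan. This holds for the detail, but it does not dispose of the point. The article chose to state an unrestricted correction, a general threshold and a sizing alpha, and as stated they do not determine one criterion. The primary visit is part of the endpoint definition, and the article states the endpoint in two places without it.

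**Conclusion.** The point holds as one of an undefined rule. The Bonferroni sentence has no family or level, it stands beside a general p < 0.05 rule and a sample size that uses the full 0.05 once, and neither post-baseline NIHSS visit is primary. The success criterion is therefore open to choice after the results are seen. That conclusion rests on the text alone.

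The effect on power arises only if the correction includes the primary test, and its size depends on the number of tests, which is assumed here. On the plan's inputs with 26 evaluable per arm, the fall is from 89% to about 83% for two tests or 64% for nine. Over the other combinations of SD and analysed number, power ranges from 90% to 96% for two tests and from 77% to 89% for nine. Two tests may thus cost little; nine would leave power below 90% in every case computed by noncentral t.

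**What to change.** 1. Name the between-group difference in NIHSS at Day 10, the end of treatment, as the single primary test at two-sided 0.05 without correction. This is the single comparison at full alpha that the sample size assumes.
2. Make Day 5 NIHSS a secondary outcome.
3. Replace the unrestricted Bonferroni sentence with a Holm procedure within a named list of secondary outcomes, one time point each. Holm controls the same error rate and is uniformly more powerful than Bonferroni.
4. Label all remaining comparisons exploratory.
5. State that p < 0.05 applies to the primary test and to the adjusted secondary p-values.

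This takes a few sentences and no extra patients, and should be settled before any unblinded data are seen. The downside is that secondary claims become slightly harder to make. If the sponsor does want the primary test inside the correction, the number of tests must be stated and the trial re-sized at the adjusted level.

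### Bonferroni is a valid correction, but Holm's step-down procedure keeps the same 5% family-wise bound and never rejects fewer hypotheses, so it is a cheap optional improvement

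*Protocol article*

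**What the plan says.** In the protocol article, the section Data monitoring and statistical analysis sets a general threshold (p below "0.05 will indicate statistically significant differences") and then adds: "We will implement the Bonferroni correction during statistical analysis to rigorously control Type I error rates". Control of Type I error is the only purpose it gives. It names neither the family of tests nor the divisor.

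The abstract has one primary scale ("The primary outcome is NIHSS score") and eight secondary outcomes: "The secondary outcomes: BMI and mRS scores, the level of TNF-A and IL-1B in serum, vascular endothelial growth factor (VEGF), Endocan ES, CD14+ and CD14"-. BMI here is evidently the Modified Barthel Index of the section Secondary results. The eight are therefore that index, mRS, TNF-α, IL-1β, VEGF, ES, CD14+ and CD14-.

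The Sample size section rests on NIHSS alone ("With α = 0.05, β = 0.1, and a bilateral test"). It gives no effect size, correlation or power for any secondary outcome.

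**The concern.** Single-step Bonferroni holds every test to α/m, where m is the number of tests in the family. Holm applies α/m only to the smallest p-value and relaxes the threshold after each rejection, yet the family-wise error stays at or below α. For the one purpose that the protocol gives, Holm therefore meets the same bound and can find more.

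At stake is power on the mechanism questions. Six of the eight secondary outcomes are blood markers, and the Discussion expects them to move together: inflammatory factors and ES down, VEGF and the CD14 subsets up. If that hypothesis is right, several effects are real at once, and that is the situation in which Holm gains. The trial was not sized for these outcomes, so any power they have is incidental.

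**Working it through.** **1. The plan's own figure.** Inputs from the Sample size section: difference 12.61 − 7.53 = 5.08, SD 5.62, two-sided α = 0.05, β = 0.1.

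n = 2 × (1.96 + 1.28)² × 5.62² / 5.08² = 25.7, so 26 per arm. Then 26 / 0.8 = 32.5, so 33 per arm and 66 in all. The figure reproduces. It concerns NIHSS only. If 20% are lost, about 33 × 0.8 = 26.4, that is 26 per arm, remain.

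**2. Does Bonferroni do its job?** With m = 8 the threshold is 0.05 / 8 = 0.00625. For eight independent true nulls the family-wise error is 1 − (1 − 0.00625)⁸ = 0.049, against 1 − 0.95⁸ = 0.337 unadjusted. It does.

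**3. Why Holm never rejects fewer.** Order the p-values and compare the smallest with 0.05/8, the next with 0.05/7, and so on up to 0.05/1, stopping at the first failure. No threshold is below 0.05/8, so every hypothesis that Bonferroni rejects is also rejected by Holm. The 5% bound holds under any dependence. The same argument applies for any m.

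**4. Size of the gain.** The documents give no effect sizes or correlation for the secondary outcomes, so these are assumed: eight two-sided z-tests, common correlation 0.3, d = 0.8 for each real effect.

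Bonferroni power per real effect has a closed form. The critical value at 0.00625 two-sided is 2.734.
- 33 per arm: 0.8 × √(33/2) = 3.250; Φ(3.250 − 2.734) = Φ(0.516) ≈ 70%.
- 26 per arm: 0.8 × √(26/2) = 2.884; Φ(2.884 − 2.734) = Φ(0.150) ≈ 56%.

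Holm's power was simulated under the same model. Average power per real effect:

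| Per arm | Real effects of 8 | Bonferroni | Holm |
|---|---|---|---|
| 33 | 8 | 70% | 82% |
| 33 | 5 | 70% | 75% |
| 33 | 2 | 70% | 71% |
| 33 | 1 | 70% | 70% |
| 26 | 8 | 56% | 68% |
| 26 | 5 | 56% | 61% |

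**5. Sensitivity to the assumed effect** (33 per arm, correlation 0.3). With all eight real: d = 0.6 gives about 38% and 47%; d = 0.4 gives about 13.5% and 15.7%. With five real at d = 0.5: 24.1% and 26.1%.

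Over a wider grid (26 or 33 per arm, d from 0.5 to 0.9, correlation 0 or 0.5) the gain was below 0.1 point with one real effect, about 0.3 to 1.1 points with two, 0.7 to 3.7 points with four, and about 2 to 14 points with all eight. The chance of finding at least one real effect differed by no more than 0.1 point throughout.

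**6. Actual family-wise error.** With five of eight real, d = 0.8, 33 per arm and correlation 0.3, it is about 1.8% for Bonferroni and 3.6% for Holm. Both are within 5%.

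**The case against.** The strongest reply is that nothing here is wrong. Bonferroni is standard, prespecified and controls the error as promised. The protocol promises no power for secondary outcomes, and the detailed procedure for them may stand in an analysis plan that is not shown. All of that stands, and it is why this point is only an improvement.

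The assumed family is also open to challenge. The section does not tie the correction to the eight secondary outcomes. It could equally govern comparisons between time points, since NIHSS and the blood markers are measured on Days 1, 5 and 10 and repeated-measures ANOVA is planned. In that case the figures for eight tests do not apply. The argument that Holm never rejects fewer does not depend on the family.

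A reader might infer that Bonferroni gives up power for nothing, or that real effects will be missed. The documents support neither. Bonferroni offers simple matching simultaneous confidence intervals, and its actual family-wise error is lower when some effects are real (1.8% against 3.6% in step 6). The loss is negligible if only one or two outcomes respond. A striking contrast, such as an 18% against 52% chance of detecting all eight effects, needs every outcome real at d = 0.8 and no dropout. With 26 per arm it becomes 8% against 32%.

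**Conclusion.** The point holds as a modest, optional gain in efficiency. That Holm keeps the 5% bound and never rejects fewer hypotheses is certain and needs no assumption about the trial. The size of the gain is conditional on the family being the eight secondary outcomes and on the assumed d and correlation. At d = 0.8 it is about 12 points of average power if all eight effects are real, about 5 points if five are, about 1 point if two are, and none if one is. It shrinks at smaller effects. The primary NIHSS comparison and its sample size are unaffected.

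**What to change.** In Data monitoring and statistical analysis, replace the Bonferroni correction by the Holm step-down procedure at family-wise two-sided 0.05 for the secondary outcomes, and report Holm-adjusted p-values. Naming the secondary outcomes in that sentence also states the family to which the adjustment applies.

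The change costs one phrase, needs no further data or patients, and can be computed by hand. The downside is that simultaneous confidence intervals matching Holm are less simple than Bonferroni's. If such intervals are a priority, keeping Bonferroni is defensible. The choice should be made before any comparison by group is seen.
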